The online training intervention will be run in small groups with unit leaders (about 15 participants in each training group). Tutors (1/group) with an academic and/or healthcare professional background will follow participants’ and their team’s learning process in each small group. Tutors will receive centralised training on the study requirements through a total of 4 h of hands-on training sessions. These sessions will cover topics related to the tutor’s role, which includes carefully monitoring participants’ engagement (returned tasks and course drop-outs, peer discussions, and any other activity), answering practical questions related to the course via group chat and/or email, and giving feedback on all course assignments. Although no makeup sessions will be organised if a participant misses a training session, individual participants (or the tutor) may still request extended time to complete their tasks. However, a unit leader can choose to stop participating in the online course at any time, for any reason, without staff needing to withdraw from the entire study (i.e. the staff can still provide follow-up data). A student may be removed from the online course if, for example, they behave unethically towards other students. At the beginning of the course, the ethical guidelines regarding online education will be presented.

In line with the Finnish National Board on Research Integrity (TENK) guidelines [28], no compensation or reimbursement will be paid to the study participants. No additional support, training, or mentoring related to leadership skills will be offered by the research team after the intervention period.

Details of the assumptions and intervention mechanism, pedagogical approaches, learning process, structure, and content of the course are described in the intervention protocol [17]. In addition, the structure and content of the intervention are described in Additional File 2 using the GREET checklist [16].

No specific activities will be organised for the passive control group participants.

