Further, feasibility and fidelity of the intervention will be assessed after course completion (month 7): [1] the number of total logins to each module (*n*); [2] the number of participants who logged in to each module (*n*, %); [3] adherence to the course, measured by the number of returned course tasks out of all possible tasks (*f*, %); [4] adherence to the course tasks, measured by the number of participants who returned course tasks for each module (*n*, %); [5] drop-out from the intervention, measured by the number of participants who leave the intervention early; [6] drop-out from the study, measured by the number of participants who leave the study early.

None of the content of the participants’ learning material, self-reflections, or peer discussion data on the Moodle platform will be analysed in this study.

Important protocol modifications will be communicated to the relevant parties, including the Ethical Review Board and the study organisations. Any modifications will be reported in the trial registry (ClinicalTrials.gov) and in the final report.

Outcomes, instruments, and specific timelines for each outcome assessment are described in Fig. 1.

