### Blinding and masking

The investigators who will enrol the units (clusters) will not be able to foresee the assignment. The allocation for each site will be kept blinded, and the staff of each unit will complete the baseline data collection before unit randomisation. When the training coordinator is ready to implement the training for the staff, the statistician will send the allocation groups by email directly to the training coordinator.

Due to the type of intervention, allocation results will be unmasked after randomisation to the unit leaders, contact persons for each unit, staff of the units, the training coordinator, and the researchers participating in the intervention design and implementation; this will reflect a real-world situation.

The leaders whose units are randomised to the intervention group will be registered on the Moodle platform by the training coordinator. Investigators running the preliminary analysis for the Data Management Committee (DMC) will be masked to data until investigators release the database. The statisticians will be masked to unit allocation in each arm.

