Data analysis will be carried out on an intent-to-treat (ITT) basis; every effort will be made to collect outcome data from all participants, regardless of whether they completed the intervention. Assumptions of normality of the residuals will be investigated. The characteristics of the units and respondents (staff members) will be summarised with descriptive statistics for each group. The specific metric will be the change between the baseline score and the final score at 7 months. The method of aggregation or the summary statistics will be based on the type of outcomes. Mean score will be used for score measurement such as the EBPQ, self-esteem, self-efficacy, and EBP scales. The Quality of care and Work absence and intention to leave will be summarised using both count and proportions.

All individuals within the cluster will be included in the trial. Possible duplicate measurements will be identified using participant ID codes, email addresses, or monitoring records.

A descriptive summary of the baseline information for both clusters and individuals will be presented first as tables of summary data. For the primary outcome EBPQ, its change from the baseline to the time immediately after the intervention (key time point) will be analysed with mixed effects linear models (respondents nested within units). In such models, the mean difference in EBPQ scores from baseline to the key point of intervention will be compared between the intervention and passive control groups, with random effects among unit leaders being estimated and characteristics of participants and units being adjusted. The changes in the subscales of the EBPQ will be analysed using multivariate mixed effects models in which simultaneous models for the three subscales are analysed jointly to overcome the inter-subscale correlation that might lead to multi-comparison bias [44]. Multiple imputations for the EBPQ and its subscales will be considered if data is missing at random. The same models will be used for the secondary outcomes, such as scores on the RSE, GSE, EBP and other continuous respondent-level outcomes. For unit-level outcomes at the key point, such as death, number of reported complaints, and number of staff’s sick days, generalised linear models will be used to compare the differences between the two groups with adjustment for unit characteristics.

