Sensitivity analyses will be conducted for units in which participation in online training is low to evaluate whether intervention fidelity has any effect on the results of the primary outcome. Results will be expressed using rate ratios, odds ratios, or least-squares mean differences with corresponding 95% CIs, depending on the type of outcome.

As our study will be a cluster randomised controlled trial, its analysis requires special consideration of the correlations within and between the clusters. First, in the sample size calculation, a clustering effect was assumed and accounted for as the ICC coefficient. Second, for the primary analysis, the intracluster (intraclass) correlation coefficient (ICC) will be reported as the proportion of the total variance of the outcome that can be explained by the variation between clusters [14]. For data analysis, the mixed effects model or two-level multilevel models that consider clustering effects will be used. In the model analysis, the variation in the outcomes among clusters will be estimated and tested for significance. Third, the overall efficacy of the outcomes will be estimated after considering the clustering effects.

In addition, covariate analysis will be conducted to control for potential confounding factors in statistical modelling. Participants’ age (novice, senior) and gender (male, female, other), status (unit leader, other staff member) and the engagement of course tasks (number of returned tasks by each participant in the intervention group) will be included in the analysis.

Statistical analyses will be performed with the SAS System for Windows, version 9.4 (SAS Institute Inc) and SPSS, versions 25.0 to 27.0 (IBM Corp). Because no adjustments for multiplicity of testing will be made, only 95% CIs will be reported for the secondary outcomes.

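### The fidelity sensitivity analysis selects units on participation that arises after randomisation and only in the intervention arm, so it cannot support a causal statement about fidelity

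*Protocol article*

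**What the plan says.** The section Data management and statistical analysis sets the main analysis: "Data analysis will be carried out on an intent-to-treat (ITT) basis". Later in the same section comes the sentence at issue: "Sensitivity analyses will be conducted for units in which participation in online training is low", with the stated aim "to evaluate whether intervention fidelity has any effect on the results of the primary outcome". It gives no comparator for these units. Results are to be reported as effect estimates with 95% confidence intervals.

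Other sections show where participation comes from:

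- Blinding and masking, on timing: "the staff of each unit will complete the baseline data collection before unit randomisation". Participation therefore follows both baseline and allocation. Outcomes places the fidelity assessment at month 7, after the course.
- Blinding and masking, on access: "The leaders whose units are randomised to the intervention group will be registered on the Moodle platform by the training coordinator".
- Interventions, on the control arm: "No specific activities will be organised for the passive control group participants".
- Interventions, on leaving the course: "a unit leader can choose to stop participating in the online course at any time, for any reason". Staff of that unit can still give follow-up data.

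**The concern.** A control unit cannot be classed as low or high on participation in a course it was never offered. Selecting on participation therefore picks out part of one arm, and the other arm has no matching part.

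The selection is also unlikely to be neutral. The Background reports completion of 42% and 63.5% in two earlier online leadership courses, with non-completers in the second citing competing duties or irrelevant content. The Sample size section expects adherence problems because nursing staff are short of time and resources. A unit under that pressure may take part less and also improve less on the EBPQ, whatever the course does.

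At stake is the reading of a secondary result. A gap between low and high units could be taken as evidence that fuller delivery gives a larger effect, when selection alone can produce it.

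**Working it through.** **Inputs from the Sample size section:** difference 10 points, SD 20 (taken here as the SD of the change), ICC 0.03, 25 per unit, 6 units per arm, 80% power, two-sided 5%.

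**The plan's own figure.** Without clustering, 63 per arm are needed. The design effect is 1 + (25 − 1) × 0.03 = 1.72, which gives 108 per arm, or 108/25 = 4.3 units (normal approximation). With a t test on 2k − 2 degrees of freedom, 5 units per arm give 75.2% power and 6 give 84.4%. Six per arm is the smallest number above 80%, so the stated 12 units are reproduced. This sets the scale only; no number in the plan is disputed here.

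**Readings of the sentence.**

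- Low units dropped: a self-selected remainder of the intervention arm against all controls.
- Low units analysed alone: a self-selected subset against all controls.
- Low against high intervention units: two self-selected groups within one arm.

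None is a comparison of groups formed by randomisation. A threshold or model would not change that.

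**Size of the selection gap.** Assumptions not in the document: the 6 intervention units split 3 v 3, fidelity has no effect at all, and participation correlates ρ with a unit's underlying change.

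- Between-unit SD = 20 × √0.03 = 3.46 points.
- Expected mean of the lowest 3 of 6 normal values = −(1.267 + 0.642 + 0.202)/3 = −0.704; the highest 3 mirror it.
- Expected gap = 2 × 0.704 × ρ × 3.46 = 4.87ρ.

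| ρ (assumed) | Gap, points |
|---|---|
| 0 | 0 |
| 0.3 | 1.5 |
| 0.5 | 2.4 |
| 0.7 | 3.4 |

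**Other splits and ICCs.** A simulation with 2 low and 4 high units and a true effect of 10 in every unit gives gaps of 0, 1.4, 2.5 and 3.5 at the same correlations, while the intention-to-treat estimate stays at 10.0. At ρ = 0.5, low units against all controls show 8.3 and the arm without them shows 10.8. With an ICC of 0.10 the gaps at ρ = 0.3, 0.5 and 0.7 are 2.7, 4.5 and 6.3.

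**Precision of the 3 v 3 contrast.**

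- Variance of a unit mean = 400 × 0.03 + 400 × 0.97/25 = 12 + 15.52 = 27.52.
- SE = √(27.52 × (1/3 + 1/3)) = 4.28 points.
- 95% half-width on 4 df = 2.776 × 4.28 = 11.9 points.

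The contrast is thus open to selection bias and too imprecise for its stated question.

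**The case against.** The strongest reply is that one sentence in an article fixes no estimator, and that threshold, comparator and model belong in a full protocol or analysis plan that is not shown. This stands to the extent that their absence is not the finding. The finding is the selection rule together with the stated purpose, and each simple reading of that rule loses randomisation.

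Several further points stand:

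- The primary analysis is intention-to-treat, and staff stay in follow-up when a leader leaves the course. Nothing lets this sensitivity analysis replace the primary result.
- The size rests on an unsourced correlation and an assumed split. At ρ = 0.5 the gap is 2.4/4.28, or just over half a standard error, and the confidence interval would show the imprecision. A wide interval does not, however, remove a shift in its centre.
- Adjustment for unit and participant characteristics might reduce selection, but 6 units leave little room for it.
- Twelve units is a minimum. More units would shrink the standard error but not the bias: for a half split among many units the gap tends to 2 × √(2/π) × 0.5 × 3.46 = 2.8 points at ρ = 0.5.
- An instrumental-variable analysis with arm as the only instrument cannot test whether the effect varies with fidelity either. It answers a neighbouring question.

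A reader might infer that the trial's main conclusion is at risk, or that the sponsor intends a dose-response claim. The documents support neither: the primary analysis does not use this selection, and dose-response is never mentioned. The listing of returned tasks as a covariate, in the same section, is a separate matter and not part of this point.

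**Conclusion.** The point holds in a limited form. Selection on participation, observed after allocation and in one arm only, cannot support a causal statement that fidelity changes the primary result. As a description of how low-participation units fared, it would be acceptable. The stated aim goes further than that.

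The spurious gap is 0 to 3.4 points over assumed correlations of 0 to 0.7 (SD 20, ICC 0.03, 3 v 3 split), against a target of 10 and a standard error of about 4.3. It would be wrong to treat 2.4 points as the expected bias: the documents give no correlation, and at zero there is none. The qualitative conclusion needs only that participation may be related to a unit's prognosis, which the trial cannot rule out. This is a worthwhile low-cost improvement and not a threat to the primary analysis.

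**What to change.** Two changes to the text:

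1. Label results for low-participation units as descriptive, exploratory and non-randomised, and drop the aim of evaluating whether fidelity affects the primary result.
2. Make the adherence sensitivity analysis a complier-average (instrumental-variable) analysis of the EBPQ change that keeps all randomised units: arm as instrument, unit participation as exposure, inference at unit level. Exposure may be binary, or graded with a stated linearity assumption.

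State its limits alongside. It estimates the effect of participating and not variation of the effect by fidelity. It assumes that assignment acts only through participation, which is uncertain in an unmasked trial with self-reported outcomes. A binary cut also treats units below it as having received nothing.

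The cost is a small amount of analysis on data already to be collected, and a wide interval. As an illustration, the intention-to-treat SE is √(27.52 × 2/6) = 3.03. If 4 of 6 intervention units were assumed to participate, an intention-to-treat effect of 10 becomes 10/(4/6) = 15, and the SE rises to about 3.03 × 1.5 = 4.5, ignoring uncertainty in the participation proportion.

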#### Characteristics of the units and participants

Each unit’s clinical specialty, number of beds, and total number of staff will be collected based on unit records, with the help of the unit leaders and a contact person for each organisation. The researchers will not have access to organisational databases. The age, gender, degrees, position and length of working experience of each participant will be collected as part of baseline data.

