### Sample size

A previous study indicated a 6-point increase in the EBPQ outcome from baseline to a key time point in the intervention group and a 5-point decrease over time in the control group [35]. We assume there will be a 10-point difference in the change of the primary outcome over time between the two groups and an estimated standard deviation of 20 [36]. With a power of 80%, a 5% type I error with a two-sided test, an inter-class correlation (ICC) of 0.03, and an average unit size of 25 with a variation of 1, the estimated sample at the cluster level is 12, 6 in each treatment arm. This would mean a total of 300 participants, 150 in each arm. As in many other trials, we anticipate challenges in recruitment and adherence due to the limited time and resources of nurse staff, trial-specific issues, communication difficulties, inadequate research experience and training, and a lack of incentives [37]. We assume that if 58% of participants complete the post-intervention assessment after the online training [38], the number of staff to be recruited for the study should be 517. Generally, if the average response rate for the baseline is 42% [39], we should aim to approach at least 1,238 nursing staff. The potential number of participants needed for this study is feasible, as the data will be collected in the wide region in south Finland. The power calculation was made using PASS 15 software for a cluster randomised design.

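### Age enters the covariate analysis as a two-level factor labelled by experience, although age and length of experience are separate baseline items; the coding is mislabelled and loses a little information

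*Protocol article*

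**What the plan says.** Three places in the protocol article bear on this.

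- *Characteristics of the units and participants*: "The age, gender, degrees, position and length of working experience of each participant will be collected as part of baseline data". Age and length of working experience are two separate items.
- *Data management and statistical analysis*, primary model: a mixed effects linear model for the change in EBPQ, with "characteristics of participants and units being adjusted". The characteristics are not listed there.
- *Data management and statistical analysis*, covariate paragraph: "covariate analysis will be conducted to control for potential confounding factors in statistical modelling". The variables then named are "age (novice, senior"), gender, status (unit leader or other staff) and the number of course tasks returned. Length of working experience is not named in this list.

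**The concern.** The covariate is called age, but its two levels are experience labels. A person who entered the profession late could be senior by age and novice by experience, so two analysts could build different variables from the same sentence. An analysis plan that carried the wording over would carry the ambiguity with it.

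The wording also commits the analysis to two levels for a quantity that is naturally continuous. A two-level version explains less of the outcome than the variable it was cut from, and it leaves any imbalance within each category unadjusted. The second point bears on the purpose the protocol gives for these covariates. Only about 12 units are randomised, stratified on unit size alone, so nothing in the design balances age or experience between arms and chance imbalance is possible. What is at stake is a little precision and a slightly incomplete adjustment.

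**Working it through.** **Inputs from the protocol (Sample size).** "10-point difference in the change of the primary outcome over time between the two groups and an estimated standard deviation of 20"; "With a power of 80%, a 5% type I error with a two-sided test, an inter-class correlation (ICC) of 0.03"; "an average unit size of 25 with a variation of 1, the estimated sample at the cluster level is 12, 6 in each treatment arm"; "a total of 300 participants, 150 in each arm".

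**Assumed, because the protocol does not give them.** The correlation r between age (or experience) and the outcome, taken as 0.1 to 0.4; a normal covariate with a linear effect; the position of the split.

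**Step 1. The plan's own figure.** This concern disputes no stated number; the check only confirms the variance structure used below.
- Individual randomisation: 2 × (20 × (1.960 + 0.842)/10)² ≈ 62.8, so 63 per arm.
- Design effect: 1 + (25 − 1) × 0.03 = 1.72.
- Power from the noncentral t with 2k − 2 degrees of freedom, k units per arm: 75.2% at k = 5 and 84.4% at k = 6.

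Six units per arm is the smallest number that reaches 80%, so 12 units and 300 participants reproduce. This takes the stated variation of 1 as negligible variation in unit size. Read as a coefficient of variation of 1, it would raise the design effect to 2.47, a separate matter.

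**Step 2. Information kept by a two-level split.** For a split with a proportion p below the cut c, the share of explained variance kept is κ = φ(c)²/(p(1 − p)), where φ is the standard normal density.

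| Split | κ |
|---|---|
| 50/50 | 2/π = 63.7% |
| 30/70 | 57.6% |
| 20/80 | 49.0% |
| 10/90 | 34.2% |

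**Step 3. Effect on the treatment-effect standard error (SE).** In units of the total variance, a unit mean has variance 0.03 + 0.97/25 = 0.03 + 0.0388 = 0.0688. The individual-level part is 0.0388/0.0688 = 56%. A covariate that acts within units reduces only that part:

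SE ratio (two-level to continuous) = √[(0.03 + 0.0388(1 − κr²)) / (0.03 + 0.0388(1 − r²))]

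At r = 0.3 with a median split, the numerator is 0.03 + 0.0388 × (1 − 0.637 × 0.09) = 0.06658 and the denominator is 0.03 + 0.0388 × 0.91 = 0.06531. The ratio is √1.0194 = 1.0097. The last column uses SE = 20 × √(2 × variance/6).

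| r | Variance, continuous | Variance, median split | SE larger by | SE in EBPQ points, continuous vs split |
|---|---|---|---|---|
| 0.1 | 0.06841 | 0.06855 | 0.1% | 3.02 vs 3.02 |
| 0.2 | 0.06725 | 0.06781 | 0.4% | 2.99 vs 3.01 |
| 0.3 | 0.06531 | 0.06658 | 1.0% | 2.95 vs 2.98 |
| 0.4 | 0.06259 | 0.06485 | 1.8% | 2.89 vs 2.94 |

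With a 10/90 split (κ = 0.342), the same formula gives 0.8%, 1.7% and 3.2% at r = 0.2, 0.3 and 0.4.

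**Step 4. Effect on power.** With the noncentral t of step 1 (10 degrees of freedom) and these standard errors, power with continuous against median-split coding is 85.2% vs 84.9% at r = 0.2, 86.2% vs 85.6% at r = 0.3 and 87.6% vs 86.5% at r = 0.4. The difference is about 1 percentage point at most.

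**Step 5. Model cost.** Continuous age entered linearly uses one parameter, the same as the two-level factor. Length of experience adds one more, against about 300 respondents.

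**The case against.** The strongest reply is that this is a label to tidy, with a negligible numerical effect. Much of that stands, and several stronger readings a reader might infer are not supported.

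- *Experience is left out of the model.* Not established. The primary model adjusts for participant characteristics without listing them, and the section headed with that term includes length of experience. The covariate paragraph is introduced as an addition, so its list need not be the whole adjustment set.
- *The cut will be chosen after the data are seen.* Not supported. Cut-points and derivations are commonly left to a statistical analysis plan, which is not shown here, and *Blinding and masking* says the statisticians will be masked to unit allocation.
- *The SE is 0.8%, 1.8% and 3.4% larger at r = 0.2, 0.3 and 0.4.* That is √[(1 − r² × 2/π)/(1 − r²)], which treats all outcome variance as reducible by the covariate. It would apply here only if the covariate explained the same share of the variance between units as within them. For a covariate acting within units, the inflation is about half as large.
- *The treatment effect is biased.* It is not, by design. Coarse coding of a baseline covariate in a randomised comparison costs precision and leaves some chance imbalance unadjusted.
- *The change is free.* Not quite. It needs up to one extra parameter and a functional form, and the protocol does not say whether age and experience are recorded in years or in bands.

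It can also be said that the protocol's stated purpose is control of confounding, not precision. That is so, but a finer coding serves that purpose better too. Age and experience are probably collinear, but collinearity between two adjustment covariates does not harm the treatment estimate.

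What remains is not missing detail: the protocol positively states a two-level coding whose labels do not fit the named variable.

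**Conclusion.** The point holds as a minor improvement. The covariate paragraph fixes age as a two-level factor with experience labels, while the baseline data keep age and experience apart. The coding is mislabelled and keeps about 64% of the covariate's explained variance at best (a median split of a normal covariate with a linear effect), and less if the split is uneven.

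The cost is an SE about 0.4% to 1.8% larger for r of 0.2 to 0.4 and a median split, and about 0.1% if r is 0.1. These figures rest on the plan's ICC of 0.03, 25 respondents per unit and a covariate acting within units. The correlations are assumptions; because the outcome is a change from baseline, the true value may sit at the low end or below. Neither the sample size nor the validity of the comparison is in question. The protocol does not settle whether experience is already adjusted for in the primary model.

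**What to change.** In the covariate paragraph of *Data management and statistical analysis*, replace the two-level age factor with age as a continuous baseline covariate, or in the finest form collected. List length of working experience as its own covariate in the same form. State the functional form (for example linear) in advance, and keep novice/senior for descriptive tables only.

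The cost is one line of text, at most one extra model parameter and the choice of functional form. Both items are already part of the baseline survey, so no new variable has to be added; whether they are recorded in years should be checked.

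### Returned course tasks, a post-randomisation measure that only the intervention arm can have, are listed as a confounder covariate and are not clearly kept out of the between-arm EBPQ model

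*Protocol article*

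**What the plan says.** All of the following is in the protocol article.

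- **Principle** (Data management and statistical analysis): "Data analysis will be carried out on an intent-to-treat (ITT) basis".
- **Primary model** (same section): a linear mixed model for the change in EBPQ from baseline to month 7, with "random effects among unit leaders being estimated and characteristics of participants and units being adjusted".
- **Covariates** (same section, further down): "covariate analysis will be conducted to control for potential confounding factors in statistical modelling". The list that follows holds age, gender, status and one more item: "the engagement of course tasks (number of returned tasks by each participant in the intervention group) will be included in the analysis".
- **What that item is** (Outcomes): the feasibility and fidelity measures, assessed after the course has ended, include "adherence to the course, measured by the number of returned course tasks out of all possible tasks".
- **Control arm** (Interventions): "No specific activities will be organised for the passive control group participants".
- **Who takes the course** (Recruitment; Blinding and masking): staff answer the surveys but do not join the training, and it is the leaders who are registered on the learning platform. The Interventions section adds that leaders carry out the course tasks with their teams.

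**The concern.** A confounder of a randomised comparison would have to precede allocation. The number of returned tasks follows allocation, is a consequence of it, and is zero or undefined for every control. It is neither a baseline characteristic nor a confounder, and the stated reason for including it does not apply.

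Once it stands in a model beside the arm indicator, the arm coefficient answers a different question: what happens to people allocated to the course who return nothing. The ITT analysis is meant to estimate the effect of allocation however much of the course was completed. If this covariate reached the EBPQ comparison, the reported effect could lose much of its precision, shrink towards zero or change sign while the course was working.

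**Working it through.** **1. Design inputs and the plan's own figure.** From the Sample size section: difference 10, SD 20, ICC 0.03, average unit size 25, 6 units per arm, two-sided 5% test, 80% power.

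- Without clustering: n per arm = 2 × (1.96 + 0.84)² × 20² / 10², about 63.
- Design effect with equal units: 1 + 24 × 0.03 = 1.72.
- SE of the arm difference with 150 per arm: √(2 × 400 × 1.72 / 150) = 3.03.
- Power with 6 units per arm: 0.91 (normal test) or 0.84 (t test, 10 df). With 5 per arm the t test gives 0.75.
- If the stated variation in unit size is read as a coefficient of variation of 1, power is 0.82 with 6 per arm and 0.745 with 5 (normal test).

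Either reading leads to 6 units per arm, 12 × 25 = 300. The sample size is reproduced and this point does not affect it.

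**2. What the arm coefficient becomes.** Let T be the returned tasks, with T = 0 in controls, and let b be the slope of EBPQ change on T. Only the intervention arm can inform b. Then

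adjusted arm coefficient = ITT effect − b × mean(T in the intervention arm).

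If controls are coded missing instead, complete-case fitting removes all of them and no between-arm effect can be estimated.

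**3. Numbers.** The documents give no task counts or slopes. Assumed here: mean 6 tasks, SD 2, range 0 to 10. For each row, 2,000 trials were simulated on the design in step 1 (generalised least squares, exchangeable correlation, normal test). Power means the chance of a significant benefit.

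A separate count for every intervention-arm respondent, true effect 10:

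| Assumed role of T | Formula | Simulated mean | SE | Power |
|---|---|---|---|---|
| T not in the model | 10 | 10.0 | 3.03 | 0.91 |
| (i) Unrelated to outcome | 10 − 0 × 6 = 10 | 9.9 | 5.80 | 0.39 |
| (ii) Carries half the effect (b = 5/6) | 10 − 5 = 5 | 5.2 | 5.80 | 0.14 |
| (iii) Carries all of it (b = 10/6) | 10 − 10 = 0 | 0.2 | 5.80 | 0.02 |
| (iv) As (iii), plus 1 point per task from motivation | 10 − 16 = −6 | −6.2 | 5.79 | 0.00 |
| (v) Motivation only, 2 points per task | 10 − 12 = −2 | −1.9 | 5.79 | 0.01 |

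The estimate is negative in 85% of trials under (iv) and 63% under (v). With a true effect of 0 and 1 point per task from motivation, the formula gives 0 − 6 = −6 and the simulation −5.9.

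The loss of precision in row (i) can be checked by hand. The variance of b is about 400 × 0.97 / (150 × 2²) = 0.647. The SE is then √(3.03² + 6² × 0.647), about 5.7.

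**4. Other codings, true effect 10.**

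- Leader's count assigned to the whole unit, cases (i) to (iii): means 9.9, 4.7 and −0.1; SE about 8.9; power 0.26, 0.09 and 0.02.
- Count only on the leader's own record (one leader per unit, staff coded 0, status in the model): 10.1, SE 3.06, against 10.1, SE 3.03 without it. If leaders gain a further 10 points, the figures are 10.0 with the count and 10.4 without.

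**The case against.** **A reader might infer that the primary EBPQ model is already fixed to adjust for returned tasks. The documents do not establish this.** The covariate sentence is introduced as an addition after the primary model has been described. The section on characteristics of the units and participants lists specialty, beds, staff number, age, gender, degrees, position and experience, and tasks are not among them. The abstract says that feasibility data are analysed separately. This part of the objection stands. It does not settle the matter, because age, gender and status, which fit the primary model's participant characteristics, share one list with the task count. Even in a supplementary between-arm model, adjusting for the count as confounding control would be wrong.

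**A reader might infer that the treatment effect would vanish or reverse.** That needs a count carried by all intervention-arm respondents, and slopes that are assumptions. Staff do not take the course, so the most literal coding puts the count on leaders' records alone, and then almost nothing changes. This also stands. Yet tasks are done with the team, so giving the leader's count to the unit is a natural alternative, and the article does not choose between them.

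**Two further inferences go beyond the text.** One is that the fidelity analysis ("Sensitivity analyses will be conducted for units in which participation in online training is low to evaluate whether intervention fidelity has any effect") sets low-participation units against all controls; no comparator is given, and such detail is commonly left to an analysis plan. The other is that the count defeats the rule that "The statisticians will be masked to unit allocation in each arm". It would do so only if task data were merged before the primary analysis was finished, and no order is stated.

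**Conclusion.** The point holds as a defect in the covariate list. A post-randomisation adherence measure that only one arm can have is named as a control for confounding, against the stated ITT basis, and it is not clearly excluded from the between-arm EBPQ model.

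That the arm coefficient would stop being the ITT effect whenever the slope on tasks is not zero follows from the algebra alone. The size does not. For a true 10-point effect, under the assumed task distribution, it runs from almost none (leaders' records only), through loss of precision alone (count per respondent, unrelated to outcome), to an estimate near 0 or negative (count per respondent that carries the effect or marks motivation). It is also near 0 when the leader's count is given to the whole unit and carries the whole effect. Whether the primary estimate would be affected at all depends on a reading and a coding that the article leaves open.

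**What to change.** In the covariate paragraph of Data management and statistical analysis, delete engagement with course tasks from the covariates of every between-arm model, and state that only variables measured before randomisation may be adjusted for. Age, gender and status can stay.

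Keep task counts as descriptive fidelity data, as the Outcomes section already plans. If an analysis by adherence is wanted, describe it separately and label it exploratory. A complier-average analysis with randomisation as the instrument is one option, not a requirement, and with six intervention units it would be imprecise.

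The cost is a wording change before analysis. Sample size, data collection and conduct are unaffected.
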